**Fig. 1 Fig1:**
[figure not shown]
Schedule of enrolment, interventions, and assessments. (1) If needed. (2) Only if the dressing is changed

Direct costs of the dressings, the human resources needed for their use, and the economic cost of complications (treatments and emergency ward visits) will be assigned according to the prices in our institution and will be applied to the events of patients included in our study.

### Study outcomes

#### Primary outcome

The primary outcome is the percentage of patients in each treatment group with skin integrity at all times when the dressing has been changed. Skin integrity is a composite of the absence of blisters, erosion, erythema, maceration, swelling, wound dehiscence, and purulent exudates. All of these items are assessed by the nurse as presence or absence at the time of changing the dressing.

#### Secondary outcomes

Secondary outcomes are time to first change of dressing; percentage of patients with presence/absence of blisters, erosion, erythema, maceration, swelling, wound dehiscence, and purulent exudates; number of dressing changes needed during hospitalization; days of hospital stay; and total direct costs related to the surgical wound care.

Nurse and patient assessment questionnaires will also be assessed as secondary endpoints. The nurse’s questionnaire assesses ease of application and removal (0 to 5), and the patient questionnaire includes patient-reported pain at removal (11-point numerical rating scale) and limitations in being mobile and sitting, getting dressed and conducting personal hygiene, and resting and sleeping. Global satisfaction of nurses and patients will also be assessed. All of these assessments are 6-point rating scales (0–5) and are based on the ad-hoc questionnaires used by Springer et al. [13].

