**Methods/design:**

This is a randomized, controlled, open-label trial to compare five types of dressings used in total knee and hip arthroplasty surgical wounds. A total of 550 patients will be randomly allocated to one of the following dressings: (1) traditional occlusive dressing, (2) Aquacel Surgical^®^, (3) Mepilex^®^ Border Post-Op, (4) OpSite Post-Op Visible, or (5) UrgoTul^®^ Absorb Border. The dressing assigned is placed right after surgery. Patients will be followed up to 14 days after surgery when the dressing is definitively removed and will be tracked up to 3 months to record any late complications. During the immediate postoperative period and patient hospitalization and at the ambulatory visits after discharge, every time that the dressing is changed, nurses perform the study assessments. The main study outcome will be the percentage of patients with skin integrity at all times when the dressing has been changed. Skin integrity is a composite of the absence of blisters, erosion, erythema, maceration, swelling, wound dehiscence, and purulent exudates. Secondary outcomes include time to first change of dressing; percentage of patients with presence/absence of blisters, erosion, erythema, maceration, swelling, wound dehiscence, and purulent exudates; number of dressing changes needed; days of hospital stay; and nurse and patient satisfaction.

Differences in the main variable between each treatment group and group 1 will be tested by means of a chi-squared test or Fisher’s exact test. Subgroup analyses of diabetic and non-diabetic patients, patients with a body mass index of more than 30 or not more than 30, and type of surgery (hip or knee) are planned.

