## Background

Surgical wounds are covered to prevent bleeding, absorb the exudates, and provide a barrier against external contamination. It is recognized that not covering the surgical wound in some surgeries may increase the risk of complications [1]. Leaving the wound uncovered is especially discouraged in those patients with suboptimal conditions that do not guarantee that the skin can constitute a protective barrier [2].

Surgical wound infection is the main nosocomial infection affecting postsurgical patients [3]. In our setting, the rates of superficial wound infection in 2015 were 0.51% for total knee arthroplasty (TKA) and 0% for hip arthroplasty.

Currently, in our hospital, after orthopedic surgery, traditional occlusive dressing of sterile gauze and non-woven hypoallergenic adhesive tape is placed. In some cases, we have observed the appearance of blistering, a situation that increases the risk of infection, pain, and overall costs of the procedure [4, 5]. Surgical wounds after knee and hip arthroplasty are about 15 to 19 cm long and closed with staples, and in our center no drainage is placed. After a patient is discharged from the hospital, the staples are removed when the patient is ambulatory, 10 to 15 days after the intervention. During this period, the wound is covered.

In recent years, new wound dressings have come into the market, at increased cost, and thus it is important to assess their contribution to patients before its use can become widespread [6].

Potential postoperative complications include changes in skin integrity, such as erythema, erosion, maceration, and blistering, the last of these being considered the most important. Blistering consists of the separation of dermis and epidermis, probably caused by edema and inflammation, which usually appear after the fifth or sixth day of surgery [7], leading to increased wound pain and risk of infection. These complications reduce mobilization and thus prolong the time to recover and increase hospital stay. It has been advocated that the right placement of the wound dressing is one of the most relevant factors to avoid blistering. Other predisposing factors described in the literature are obesity, venous insufficiency, diabetes mellitus, and old age [7, 8]. The incidence of blistering described for orthopedic surgery varies from 6% to 24% [7, 9].

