### Study procedures and assessments

On the day of surgery, the nurse in the operating room will place the dressing right after the surgery, as assigned. Information on the surgical procedure, such as length of surgery, total time of ischemia, use of a layer wound closure technique, and flexion or extension of the limb when applying the dressing (for TKA), will be recorded by operating theater nurses.

After that, patients will follow the fast track and will be discharged after 48 h in case of the absence of complications that require an extended stay. A outpatient visit is performed 7 days after the intervention. During this visit, the nurse changes the dressing and assesses the wound. On day 14 after surgery, a second nurse ambulatory visit is performed to remove the dressing, assess the wound, and remove the surgical staples. Assessment of wound during the ambulatory visits is performed by two different nurses from the study team in order to minimize the inter-observer variability. According to the current clinical practice in our hospital, during the immediate postoperative period and hospitalization, dressing is changed only in those cases when the surgeon requires it because of excessive bleeding or because of the presence of any other sign or symptom that is suggestive of wound complications. If this is the case, every time that the dressing is changed, nurses will perform the study assessments (Fig. 1. “Schedule of enrolment, interventions, and assessments”). The time spent in the procedure and the number of dressings used will also be recorded. In the event of serious health complications not related to the wound, patients will be withdrawn from the study. After the definitive removal of the dressing, patients will be tracked for the following 3 months to record any late complications, by review of the clinical records in order to detect any emergency ward visit, re-consultation, or re-hospitalization. Any untoward event detected during the follow-up (14 days) and a further 3 months will be followed up to resolution. In the event of wound complications, treatment needed (i.e. antibiotics and wound debridement) is recorded. Any other complications are recorded systematically and followed until resolution.

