#### Inferential statistics

Differences in the main variable between each treatment group and group 1 will be tested by means of a chi-squared test or Fisher’s exact test. For categorical ordinal variables, the analysis of variance (ANOVA) or Kruskal–Wallis test will be used. Time to event data will be summarized by means of Kaplan–Meier curves and compared with the log-rank test. Exploratory comparisons between the different new dressings will also be performed for primary and secondary variables. Subgroup analyses in diabetic and non-diabetic patients, patients with a BMI of more than 30 or not more than 30, and type of surgery (hip or knee) are planned.

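### Secondary outcomes: time to first dressing change does not separate required changes from the scheduled day-7 change, and the count of changes stops at discharge in the Methods but not in the Abstract

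*Protocol article*

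**What the plan says.** All references are to the protocol article.

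- **Time to first change.** Secondary outcomes: "Secondary outcomes are time to first change of dressing". No distinction is drawn between scheduled and required changes. Under Inferential statistics, time-to-event data are shown as Kaplan–Meier curves and "compared with the log-rank test".
- **Scheduled change.** Study procedures and assessments: "A outpatient visit is performed 7 days after the intervention", and then "During this visit, the nurse changes the dressing and assesses the wound". This applies to all arms. The dressing is finally removed at a second visit on day 14.
- **Changes in hospital.** The same section allows these only when the surgeon asks for one, because of bleeding or signs of a wound problem. Uncomplicated patients go home after 48 h.
- **Count of changes.** Secondary outcomes: "number of dressing changes needed during hospitalization". The Abstract (Methods/design) has "number of dressing changes needed; days of hospital stay", with no restriction to the hospital stay. The Discussion also speaks of the number of cures needed without that restriction.
- **Timing of blisters.** The Background says that they "usually appear after the fifth or sixth day of surgery".

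**The concern.** The two outcomes are there to show whether a dressing needs fewer changes. The informative event is a change that someone had to make. A change that the schedule imposes on all patients says nothing about the dressing.

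In the time-to-event outcome the two kinds are merged. A patient who needs no extra change still has a first change at the day-7 visit, and its date depends on the appointment book. Taken as worded, the Kaplan–Meier curves must all drop to zero around day 7. With unscheduled changes in a minority of patients, the medians will sit at the visit day whatever the dressing does.

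The in-hospital count does consist of required changes, but over a short window: 2 of 14 dressing days (14%) for an uncomplicated patient. By the Background's own account, blistering usually comes after that window closes, so changes prompted by it would normally not be counted.

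At stake is how well the trial can show a difference in extra changes. The Discussion presents the number of cures as part of what this study adds.

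**Working it through.** **1. The plan's own figure.** No calculation is given for the dressing-change outcomes. The only computed figure is 110 per group for skin integrity (82% versus 95%, two-sided 5%, power 80%, loss 15%). With the pooled-variance formula and mean proportion 0.885:

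n = [1.96·√(2·0.885·0.115) + 0.8416·√(0.82·0.18 + 0.95·0.05)]² / 0.13² = (0.884 + 0.372)² / 0.0169 ≈ 93.4, so 94 per arm.

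94/0.85 gives 111 and 94 × 1.15 gives 109. The stated 110 is reproduced, and 94 evaluable per arm is used below.

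**2. Share of first changes that are scheduled.** The article gives no rate of unscheduled changes before day 7, so a rate p has to be assumed. The scheduled share is 1 − p: 70% to 95% for p from 30% down to 5%.

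**3. All visits exactly on day 7.** At a given time with n at risk (n₁ in the new-dressing arm) and d events, the log-rank test adds d₁ − d·n₁/n to the numerator and d·(n₁/n)(1 − n₁/n)(n − d)/(n − 1) to the variance. If everyone still at risk has the change on day 7, then d = n and d₁ = n₁, and both terms are zero. Counting the change as an event or as censoring gives the same test. Simulated z statistics agreed to within 1e-14.

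**4. Visits spread over days 6–8.** Assumptions: unscheduled change in 25% versus 10%, spread evenly over days 1–5; visits spread evenly over days 6–8; 94 per arm.

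- Unscheduled changes per day: 94 × 0.25/5 = 4.70 and 94 × 0.10/5 = 1.88, together 6.58.
- Share at risk in the new-dressing arm on days 1 to 5: 0.500, 0.508, 0.516, 0.525, 0.535 (sum 2.584). Expected events there: 6.58 × 2.584 = 17.0; observed on average 9.4. Numerator −7.6, variance about 7.95.
- Censoring at the visit: z = 7.6/√7.95 = 2.70, power ≈ Φ(2.70 − 1.96) = 77%.
- Visits counted as events: 70.5 + 84.6 = 155.1 patients remain, 51.7 per visit day, share 84.6/155.1 = 0.545. Day 6 adds variance 51.7 × 0.248 × 103.4/154.1 = 8.6, day 7 adds 51.7 × 0.248 × 51.7/102.4 = 6.5, and day 8 adds 0. The numerator gains nothing on average. The variance becomes about 23.0, z = 7.6/√23.0 = 1.58, and power ≈ Φ(1.58 − 1.96) = 35%.

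The signal is unchanged and the noise variance nearly triples.

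**5. Simulation.** 1,500 two-arm trials per scenario. The first two rows use 94 per arm and unscheduled changes on days 1–5; the others use 93 per arm and days 0–4. All rates and visit spreads are assumed.

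| Unscheduled change, control vs new | Scheduled change censored | Counted as event, visits days 6–8 | Counted as event, visits days 5–9 |
|---|---|---|---|
| 25% vs 10% | 78% | 35–38% | 26–29% |
| 20% vs 8% | 67% | 26% | 20% |
| 20% vs 5% | 90% | 37% | 29% |
| 30% vs 10% | 94% | 55% | 46% |
| 30% vs 15% | 69% | 36% | 30% |

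Ranges in the first row are from repeat runs. With equal rates (10% in both arms) the rejection rate stayed near 5% under every rule.

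**6. Which outcome captures which required change.**

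| When the required change occurs | Count, Methods wording | Time to first change |
|---|---|---|
| In hospital | yes | yes, if it is the first |
| Discharge to day 7 | no | yes, if it is the first and is recorded |
| Day 7 to day 14 | no | no, a first change has already happened |

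Under the Abstract's wording the count would cover all three rows.

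**The case against.** **No event rule is stated.** The article never says that the day-7 change is an event. Event and censoring rules commonly sit in an analysis plan, which is not shown. This stands: the reading is the literal one, and the absence of a rule is no fault in itself. What remains is an outcome worded as the first change of any kind beside a compulsory change for everyone. The window of the count is different, because it is a stated definition and the Abstract words it differently.

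**The power loss rests on assumptions.** This also stands. The visit is set at day 7 with no window mentioned, and if all visits fall on that day there is no loss. The loss needs some spread in visit days, and the rates are not from the article. The effect is dilution without false positives, on an outcome that the trial was not sized for.

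**Neither outcome measures extra changes.** A reader might infer this, but the article does not support it. In-hospital changes are by definition required and are counted, and an unscheduled first change before day 7 registers in the time-to-event outcome. Capture is partial.

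**Blister or cost data are lost.** A reader might infer this too. Blisters are assessed at every dressing change, including both scheduled visits, within the primary composite and as an outcome of their own. Total direct costs of wound care are a separate secondary outcome with no limit to the hospital stay. The timing of blisters matters here only because changes prompted by them would usually fall outside the in-hospital count.

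**The Abstract merely abbreviates.** Possibly so. But the two wordings define different quantities, and a reader cannot tell which will be reported.

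**Conclusion.** The point holds as a cheap improvement to two secondary outcomes. The primary outcome and the sample size are unaffected.

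- Time to first change, on its literal reading, mixes required changes with a compulsory one, and most events would be appointment dates. The consequence ranges from none (all visits exactly on day 7) to a loss of about half the power or more in most of the assumed scenarios: about 78% to 35–38% with visits on days 6–8, and to 26–29% on days 5–9, for 25% versus 10%. These figures illustrate and do not predict; the article gives neither the rates nor the spread. Type I error is not inflated.
- The Methods and the Abstract disagree on the window of the count. Under the Methods wording, required changes from discharge to day 14 are not counted, and those after day 7 enter neither outcome. This does not depend on the simulation.

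The article does not support saying that the day-7 change is declared an event, or that extra changes go wholly unmeasured.

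**What to change.** 1. Define the time-to-event outcome as time from surgery to the first unscheduled, clinically required change, with censoring at the scheduled day-7 change.
2. Define the count as the number of unscheduled changes from surgery to day 14. Record at the existing day-7 and day-14 visits any change made elsewhere since discharge or since the last visit.
3. Make the Abstract and the Secondary outcomes section give the same window.

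The cost is wording plus one case report form question at two existing visits, with no change to how patients are treated. Changes between visits will rest on patient report or records. The 170 patients included at the time of writing may lack these data. The other 550 − 170 = 380 (69%) could still provide them if the change were made at that point, and the report should say from when the question was asked. The censoring rule needs only the date and reason of each recorded change, so it can be applied to enrolled patients wherever these are on file.

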### Data collection and management

Study data will be collected in paper case report forms (CRFs) designed for the study. Risk-adjusted monitoring will be performed by personnel independent of the research team and will consist of checking all informed consent forms and completeness of all CRFs and source data verification for a random sample of patients. Data will be entered in the study database by the study team. Patients will be identified by a numerical code, and no personal information will be included in the paper CRF or the database.

### Statistical methods

#### Sample size

The estimation of sample size was based on the review of previous literature [11, 14]. Our hypothesis is that 82% of patients will present skin integrity with the traditional wound dressing (group 1) during the process of wound healing and that the application of any of the other dressings studied will result in 95% of patients with skin integrity. Given a two-sided risk of 5%, a power of 80%, and an expected loss of 15%, 110 patients per group are to be included. No adjustment for multiplicity has been considered, as the comparison of the different dressings with group 1 represents distinct research questions. All tests will be performed at an alpha level of 0.05.

#### Populations of analysis

The primary analysis will be performed according to the intention-to-treat principle and will include all randomly assigned subjects to whom the study dressing has been placed in the operation theater. Subjects will be considered and analyzed in the treatment group assigned. As no data imputation for missing values has been considered, only patients with available assessments of the main outcome will be considered in the main analysis. The final populations of analysis will be defined before the statistical analysis, and criteria will be applied to all patients regardless of the arm they have been assigned to.

#### Descriptive statistics

Patient characteristics will be described by treatment group and for the entire sample of patients. Quantitative variables will be presented as means and standard deviations or, in cases of skewed distribution, as medians and inter-quartile ranges. Categorical variables will be presented as absolute and relative frequencies.

#### Inferential statistics

Differences in the main variable between each treatment group and group 1 will be tested by means of a chi-squared test or Fisher’s exact test. For categorical ordinal variables, the analysis of variance (ANOVA) or Kruskal–Wallis test will be used. Time to event data will be summarized by means of Kaplan–Meier curves and compared with the log-rank test. Exploratory comparisons between the different new dressings will also be performed for primary and secondary variables. Subgroup analyses in diabetic and non-diabetic patients, patients with a BMI of more than 30 or not more than 30, and type of surgery (hip or knee) are planned.

### Feasibility

The number of TKAs and THAs following fast track was about 421 in 2016. Recruitment of patients started in April 2017 and is anticipated to end in April 2019. An investigator team composed mainly of nurses has been trained in all study procedures and is in charge of tracking and assessing the patient throughout the process, from ambulatory setting, operating room, and hospitalization.

### Ethics

This trial is being conducted in accordance with the Declaration of Helsinki and good clinical practice principles. The study protocol (version 1, December 2016) was approved by the research ethics committee of our center (*Comité Ético de Investigación Clínica de la Corporació Sanitària Parc Taulí*) in January 2017. The protocol has been registered at ClinicalTrials.gov (NCT03190447). Written informed consent will be obtained from each participant before any trial-related procedures are carried out. The present study protocol has been written in accordance with the Standard Protocol Items: Recommendations for Interventional Trials (SPIRIT) 2013 statement for reporting a clinical trial protocol [15]. The SPIRIT checklist is provided in Additional file 1.

## Discussion

We have designed a randomized clinical study to compare four new wound dressings with the traditional one in patients undergoing programmed TKA or THA in terms of skin integrity during the postoperative period. Additional endpoints addressing patient satisfaction, ease of application/removal, and costs will be included. Pre-formed wound dressings are medical devices. They are approved for marketing with little evidence of their comparative benefits regarding alternatives already existing in the market. Therefore, the choice of the dressing is guided mainly by theoretical properties and personal experiences of its use. Thus, there is a need to generate robust and unbiased evidence of the potential advantages of these new dressings with respect to the conventional ones before extending their use to clinical practice. It is also relevant to evaluate the costs associated with their acquisition and with the outcomes. For the latter part, a cost analysis is also planned.

In our study, we will assess four different dressings. Although no formal comparisons among the new dressings will be carried out, it is relevant to include four of the most used pre-formed dressings in our setting in the same study as it will provide indirect comparisons of the advantages and disadvantages of each of them. We consider this an efficient design. According to the review by Sharma et al. [11], most studies compare only two dressings and most do not compare the new ones with the traditional ones that represent a lower cost for the hospital. Only two studies compared more than two dressings [9, 16].

We also intend to perform a subgroup analysis that could provide information on the differential efficacy of each dressing in different types of surgery or types of patients.

One of the main limitations of the study is the lack of blinding. The implementation of alternative procedures to guarantee the blind assessment (such as a blind evaluator) is feasible and desirable [17]; however, this was considered to be logistically too complicated and unfeasible. Although the assessments are performed by nurses and thus could be subject to subjectivity, the assessment of the presence of blister, erythema, and other endpoints will be assessed as a dichotomous variable, being less prone to bias. Assessments may also be biased by inter-observer variability. To overcome this problem, only two nurses on the team are responsible for the assessments during the scheduled ambulatory visits. However, when an unscheduled changing of dressing is carried out during hospitalization, assessments are performed by a variety of nurses, and although they are all trained in the study procedure, the inter-observer variability cannot be ruled out.

We chose, as the main endpoint, a composite variable, including any aspect of the skin that compromises skin integrity. Although this is an artificially built variable, we think it may provide good information on skin integrity. All components of the variable will also be considered as secondary variables and thus no information will be lost. Although the presence of blistering is the most frequently used primary endpoint in clinical trials comparing wound dressings, some authors have also used the concept of wound complication, including blisters, inflammation, leakage, and maceration, in a composite endpoint [13, 16].

We also included outcomes related to comfort, preferences and ease of manipulation by the nurse, time spent on the cure, and number of cures needed. These variables have not been considered in most studies and thus we consider that they add value to this investigation. Studies including these types of measures have shown the impact of the different dressings on the well-being of patients and on overall costs [4, 18, 19]. Surgical procedures may also have an impact on the outcomes measured in this trial. Factors related to surgery that influence wound healing, such as duration of surgery, total time of ischemia, and use of a layer wound closure technique, will be recorded.

The fact that this is a single-center study may be a drawback for the external validity of the results. Our hospital has very low rates of infection reported in recent years and thus it is expected that few infections will be registered in this study. The incidence of other complications such as hemorrhage is not routinely monitored but could be different from other hospitals because of the techniques used in our setting (i.e. the lack of use of Redon). Also, it has to be taken into account that we will only include patients undergoing fast track, with early mobilization and without major complications before surgery, and this is a population in which low rates of complications are expected.

Our main question is whether any of the modern dressings, all of which claim different advantages, is better than the conventional one (traditional occlusive dressing of sterile gauze and non-woven hypoallergenic adhesive tape) that is used as a standard in this type of surgery in our institution and that is cheaper than any of the pre-formed ones. We hypothesize that any or at least some of them are better and that these advantages would justify its use even if the direct costs are higher. As no differences in terms of skin integrity are expected among the new dressings, only exploratory comparisons for the primary endpoint will be performed among them. We foresee that differences between new dressings in secondary endpoints (ease of application and comfort) may be found and also differences depending on the type of surgery (hip or knee) and characteristics of patients (BMI and presence of diabetes). The large sample size will allow us to explore all of these characteristics, and all of these analyses will generate hypotheses. Thus, we consider that this strategy for the analysis will offer more advantages than other strategies based on post-hoc analysis to check where the differences are.

Finally, patients included in this study constitute a large cohort of patients undergoing arthroplasty procedures. Data on the clinical course of these patients and their complications will also be analyzed to explore factors that may be related to better clinical results.

The results of this study will be useful for decision making and not only will give us information on whether the dressings studied contribute to a better outcome of the wound compared with traditional dressings but also may allow us to decide which dressing will offer better results depending on the characteristics of patients.

